#### Adherence

Adherence with the exercise program will be assessed and noted by the therapists using the participants treatment files. At the end of the intervention, the adherence with home exercises program after discharge will be measured using the following ordinal scale; How often did you perform home exercises? 1) none of the time, 2) some of the time, 3) most of the time, 4) almost all of the time, 5) all of the time) [61].

#### Co-interventions

Participants will be asked to report any type of co-interventions (e.g., osteopathy, chiropractic, massage therapy) during the intervention period at the end of the study. Pain medication will be allowed as it would be unethical to withhold medication, but this information will be collected for all participants.

#### Data integrity

The database will be saved and maintained on a secured network at the institution. Any inconsistencies in the data will be reported, explored and resolved. Only study personnel will have access to the password-protected database. Investigators will allow verification of the data from the ethics board and maintain adequate and accurate records of all documents. Any modifications to the protocol will be reported and communicated to the REB. Confidentiality of the data will be protected and maintained during and after the trial. Data will be stored at Concordia University for a minimum of 5 years after the study closure.

### Sample size calculation

Sample size calculation was determined by using the effect size (e.g., significant pre-post difference in multifidus muscle CSA measurements following a motor-control exercise intervention) from a previous study^62^ (e.g., previously reported effect size (95% CI) for each spinal level; L2 = 0.87(0.20,1.54); L3 = 0.90 (0.19,1.62); L4 = 1.00(0.32, 1.67), and L5 = 0.81(0.10,1.53)) [62]. The mean effect size (over the 4 different spinal levels) was calculated and used for sample size estimation. Pre-post results were considered as independent (independent from two groups) to concur with the present study statistical analysis (between-group factor). Therefore, sample size estimation was calculated with the G*power software (mean difference, independent t-test) on the basis of a mean effect size d = 0.90, 80% power and a significance level of alpha 0.05, and allowing for a 10% lost to follow-up and 10% treatment non-adherence.

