## Background

Low back pain (LBP) is one of the leading causes of disability worldwide [1, 2], costing billions of dollars in Canada alone each year, including health care costs and missed work [3]. While chronic LBP is a prevalent and persistent global burden, up to 90% of the North American population alone, is at risk of developing LBP [3–5]. Of these cases, only 10% are thought to be the result of identifiable radiological characteristics, such as nerve root compression, fractures, or stenosis [6]. The remaining cases are classified as non-specific LBP, which unsurprisingly, present with a variety of clinical manifestations without diagnostic or therapeutic options. LBP is significantly associated with high levels of disability, decreased function and participation in life as well as decreased sleep quality and increased depressive symptoms [7–9]. Currently, exercise therapy is the most common conservative treatment for LBP as it is easily accessible and can be individually tailored to patient’s needs [10]. Exercise has been bound to improve pain, quality of life and psychosocial aspects of pain such as pain-related fear (catastrophizing), kinesiophobia, depression, and anxiety [11–13]. Although exercise is more effective than no intervention, the effect size of exercise are small to moderate, and to date there is no evidence that one exercise approach is superior to another [14–16].

Individuals with LBP are more likely to have muscle atrophy, fatty infiltration, and asymmetries of the lumbar musculature, specifically the multifidus muscle [17–19]. Possible mechanisms for degenerative muscle changes include poor motor control, decreased muscle activation, and fatigue. Loss of motor coordination can lead to repetitive mechanical stress on surrounding structures, increasing the risk of instability, joint overloading, and pain [20]. Therefore, exercise interventions usually target the lumbar paraspinal muscles specifically [15, 16].

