There is mixed evidence as to whether current exercise interventions actually results in morphological changes in the paraspinal muscles (e.g., hypertrophy, reversal of fatty infiltration) and whether paraspinal muscle physiological adaptations will translate in better improvement in patient-related outcomes [21–24]. A recent preliminary study examined the effect of a resistance-based exercise protocol on the cross-sectional area (CSA) and fatty infiltration for both the erector spinae and multifidus muscles [22]. The intervention did not yield any significant morphological change but the investigators suggested further exploration into identifying what types of resistance exercise works best. While another recent study reported decreased in paraspinal muscle fatty infiltration following a 16-week free-weight-based resistance training intervention without isolated lumbar extension exercise [23]. In recent years specific motor control interventions have gained popularity given its focus on retraining control of trunk muscles activation, alignment and movement in order to restore proper function [16]. Motor control exercises often target paraspinal muscles directly however, there is limited evidence on their effectiveness in improving spinal muscle morphology [21, 22].

Previous studies that have used targeted strengthening exercises to improve lumbar muscle strength recommend using exercises that include increased pelvic restraints which limit the activity of other large muscles of the posterior chain (e.g., gluteus and hamstrings) [15, 25]. Since most studies do not include exercises where the pelvis is stabilized it is possible that the lack of morphological changes observed in spinal muscles may be due to the compensation of the other posterior chain muscles [25]. Further studies are needed to examine whether pelvic stabilization during extension exercises is able to effectively target the lumbar extensors and lead to significant morphological and functional changes. Furthermore, we are also aware of only one previous study that has examined the correlation between changes in lumbar muscle morphology with fear avoidance and psychosocial factors [22]. High fear avoidance in patients with chronic LBP is significantly associated with less improvement in disability after 1 year as well as longer sick leave [26]. As such, controlling for factors that could influence the change in disability is crucial.

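### The sample size enters a within-group pre-post effect (d = 0.90) as the difference between two active exercise arms, so the stated 80% power rests on an unstated assumption of no change in GE

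*Protocol article*

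**What the plan says.** The Sample size calculation section of the protocol article describes its effect size as a "significant pre-post difference in multifidus muscle CSA measurements following a motor-control exercise intervention", taken from one previous study. The level-specific values are "L2 = 0.87(0.20,1.54); L3 = 0.90 (0.19,1.62); L4 = 1.00(0.32, 1.67), and L5 = 0.81(0.10,1.53". They are averaged to give a "mean effect size d = 0.90, 80% power and a significance level of alpha 0.05". On the step from within-group to between-group it says "Pre-post results were considered as independent (independent from two groups) to concur with the present study statistical analysis (between-group factor", and then "sample size estimation was calculated with the G*power software (mean difference, independent t-test". The total is inflated by "allowing for a 10% lost to follow-up and 10% treatment non-adherence". The resulting trial has 50 participants, 25 per arm (Procedure).

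The comparator is active. Under Procedure and General exercise group (GE), these participants attend two supervised sessions a week for 12 weeks, with three sets of each resistance exercise and rising loads. The Statistical analysis section plans a repeated measures ANOVA with a between-subjects factor for the primary and secondary measures.

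**The concern.** The trial estimates the change in MC + ILEX minus the change in GE. The number used to size it is the change after one motor-control programme, with no comparator subtracted. The two are equal only if the comparator arm stays where it started.

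The article openly says that the effect is pre-post and was handled as two independent groups. It does not say what this implies for GE. Its Background leaves that implication open to doubt. It calls the evidence on morphological change mixed. It cites one resistance programme with no significant change in size or fat content, and another study that "reported decreased in paraspinal muscle fatty infiltration following a 16-week free-weight-based resistance training intervention without isolated lumbar extension exercise". The second result concerns fatty infiltration, not CSA, but fatty infiltration is part of the primary outcome. On exercise in general, the Background adds that "to date there is no evidence that one exercise approach is superior to another".

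The Discussion sets out to learn whether MC + ILEX is superior to GE. If the arms do not differ significantly, readers will weigh that result by the claimed 80% power. That figure belongs to a different contrast.

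**Working it through.** **Inputs.** Effect sizes, d = 0.90, 80% power, alpha 0.05 and the 10% + 10% allowance come from Sample size calculation; 25 per arm comes from Procedure. Two-sided testing is assumed, since the article does not state sidedness and a one-sided test does not lead to 50 (16 per arm; 32/0.8 = 40).

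**1. Reproducing the plan's figure.**
- Mean effect: (0.87 + 0.90 + 1.00 + 0.81)/4 = 0.895, rounded to 0.90.
- Normal approximation: n per arm = 2(1.96 + 0.84)²/0.90² = 19.4, so 20 per arm; 40/0.8 = 50.
- Exact noncentral t: 21 per arm (81.2% power); 42 × 1.2 = 50.4.

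N = 50 follows from the stated inputs. The arithmetic is sound; the question is what d = 0.90 represents.

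**2. Power of the same calculation when GE changes.** Take 20 analysable per arm (25 × 0.8) and MC + ILEX at 0.90 SD. The between-arm difference is d = 0.90 − g, where g is the GE gain in SD. Power comes from the noncentral t with 38 degrees of freedom and noncentrality d√(20/2). The article gives no value of g, so these are assumptions.

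| GE gain g | d | Power |
|---|---|---|
| 0 | 0.90 | 79% |
| 0.1 | 0.80 | 69% |
| 0.2 | 0.70 | 58% |
| 0.3 | 0.60 | 46% |
| 0.45 | 0.45 | 28% |

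The difference detectable with 80% power is 0.91 SD at 20 per arm and 0.89 SD at 21, in effect the whole pre-post gain of the source study. With all 25 per arm analysed it is 0.81 SD, which leaves room for a GE gain of about 0.90 − 0.81 = 0.09 SD.

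**3. What the planned analysis would change.** A repeated measures comparison uses the baseline to 12-week correlation r. Simplify to those two time points and suppose 0.90 is in cross-sectional SD units (the article does not say). The SD of a change score is then √(2(1 − r)), so the detectable difference is 0.909 × √(2(1 − r)). With baseline adjustment it is about 0.909 × √(1 − r²). Again 20 per arm:

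| r | Detectable, change score | Detectable, baseline-adjusted | Power on change scores, g = 0 | Power on change scores, g = 0.3 |
|---|---|---|---|---|
| 0.3 | 1.08 SD | 0.87 SD | 65% | 35% |
| 0.5 | 0.91 SD | 0.79 SD | 79% | 46% |
| 0.7 | 0.70 SD | 0.65 SD | 95% | 67% |
| 0.8 | 0.57 SD | 0.55 SD | 99% | 83% |
| 0.9 | 0.41 SD | 0.40 SD | over 99% | 99% |

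For change scores, the independent-groups calculation corresponds to r = 0.5. Above that the trial has more power than step 2 shows; below it, less.

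**4. Non-adherence.** If non-adherers are analysed as randomised, only loss to follow-up removes people: 25 × 0.9 = 22.5, so 22 per arm. If 10% of MC + ILEX then gain nothing, d = 0.9 × 0.90 = 0.81. Power is about 75%, even with no GE gain.

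**The case against.** The strongest reply is that the planned analysis is not the t-test used for sizing. If multifidus CSA is strongly correlated within a person, a repeated measures analysis could keep 80% power despite a real GE gain: at r = 0.8 on change scores, a GE gain of up to about 0.90 − 0.57 = 0.33 SD. MC + ILEX also adds isolated extensor training to motor control and might gain more than 0.90 SD. This much stands. A reader might infer that 80% power is attainable only if GE does not change at all, or that the trial is underpowered. The documents support neither, because they give no r, no SD unit and no expected GE change. Equally, the article does not rely on a high r, so its 80% cannot be defended by one, and at a low r the position is worse than stated.

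A small GE change in CSA is also arguable. The Background cites a null resistance study and suggests that without pelvic restraint other posterior-chain muscles may take the load; Table 1 lists no lumbar extension exercise. That would be a case for assuming little GE gain, but the sample size section does not make it.

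Three further inferences should not be drawn. The article does not say the source study had a single arm, only that the effect used was pre-post. It does not say non-adherers will be excluded; it only inflates N for them, and analysis sets may be defined in an SAP that is not shown. The wide intervals around the source effects concern its precision, which is a separate matter.

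**Conclusion.** The point holds for the calculation as published. A within-group change has been used as a between-arm difference against an active comparator, and the 80% depends on an undeclared assumption of no GE change with MC + ILEX at 0.90 SD. On that calculation, modest assumed GE gains of 0.1 to 0.3 SD reduce power to between 69% and 46%, and a gain of half the MC + ILEX effect reduces it to 28%. These figures rest on two-sided 0.05, 20 analysable per arm and an unadjusted t-test. They show how sensitive the claim is; they do not predict the power of the planned analysis, which cannot be determined without r. The fault lies in the justification and the claim attached to n = 50, not in the arithmetic.

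**What to change.** Keep n = 50 and rewrite the Sample size calculation section:

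1. Say that 0.90 is a within-group change, give its SD unit, and state that the 80% figure assumes no change in GE.
2. Replace the power claim with the between-arm difference in change detectable with 80% power at 20 per arm under the planned analysis, over a stated range of r. On change scores in cross-sectional SD units this is about 1.08, 0.91, 0.70, 0.57 and 0.41 SD at r = 0.3, 0.5, 0.7, 0.8 and 0.9; it is smaller with baseline adjustment, should that be adopted.
3. Show power across assumed GE gains, for example 0 to 0.45 SD, labelled as assumptions.
4. Say how non-adherers are analysed. If as randomised, count only loss to follow-up as attrition and report the diluted power (about 75% at 22 per arm with d = 0.81 under the unadjusted test).

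This needs rewording and a short table, with no extra participants and no change to outcomes or randomisation. The downside is that the stated power may look less favourable.

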### Statistical analysis

Descriptive statistics for demographic characteristics and outcomes will be calculated. The pre to post intervention changes in primary and secondary measures will be evaluated with the use of a between-subjects repeated measures ANOVA. Linear mixed models will be used to assess whether baseline psychological scores can modify the response to the exercise therapy treatment. A *p*-value of < 0.05 will be considered statistically significant.

### Dissemination of findings

The results of this trial will be published in peer-reviewed journals and presented at conferences. After publication of manuscripts, data request can be submitted to the principal investigator (MF).

## Discussion

LBP is one of the most disabling diseases and a major health issue. In accordance with the ever-increasing body of evidence demonstrating accelerate atrophy and fatty infiltration in patients with chronic LBP, improving strength, function and control of the trunk muscle through therapeutic exercises is a primary goal in physical rehabilitation of patients with LBP. As such, strengthening, lumbar stability, and motor control exercises are recommended and amongst the most popular exercises for the management of chronic LBP [14–16, 63]. If specific targeted lumbar muscle exercises are to be prescribed and used clinically, the evaluation of physiological muscle changes, such as hypertrophy and reversal of fatty infiltration and whether they mediate improvements in functional status should be considered when assessing the effectiveness of different exercise interventions. This trial aims to investigate whether MC + ILEX has any superiority to GE in improving overall paraspinal muscle health and related clinical symptoms. Our research protocol through measurement of muscle morphology and function, clinical symptoms and psychological factors will shed some light into this field. The results of this trial are expected to improve the efficacy of prescriptive exercise training in subjects with non-specific chronic LBP.

The limitations of this study include the use of only two recruitment locations, which primarily represents the anglophone population of Montreal. This will decrease the generalizability of this study. We are also restricting inclusion to those able to understand and read English or French, which will also limit generalizability. Furthermore, true blinding of exercise supervisors/providers is not possible within an exercise trial. However, the participants will not be told their group assignment and only that they are completing an exercise protocol with the aim of decreasing their LBP and increasing their function.

## Data Availability

Not applicable.

## Abbreviations

LBP: Low back pain
ODI: Oswestry disability index for low back pain
GE: General exercise
MC + ILEX: Motor control and isolated lumbar extension exercise
